## Abstract

**Introduction:**

Hand eczema (HE) is one of the most common skin disorders and an important cause for morbidity and occupational disability. The 1-year prevalence of HE is estimated to be up to 10% and it is estimated that 5%–7% of those develop severe chronic HE. However, current clinical evidence is not compelling enough to guide clinical practice. In a survey among 194 UK dermatologists the most frequent first choice approaches were psoralen combined with ultraviolet A (UVA) treatment (PUVA), oral steroids and alitretinoin (AL). When asked which strategy was most efficient for long-term outcome 20% of clinicians indicated they did not know; 43% of clinicians reported AL and 30% reported PUVA.

**Methods and analysis:**

ALPHA is a multicentre, open, prospective, two-arm parallel group, randomised controlled trial comparing PUVA and AL with a planned sample size re-estimation. Between 500 and 780 participants will be randomised on a 1:1 basis. The physician’s global assessment (PGA) will direct treatment after randomisation, non-responders will be treated according to usual clinical practice; providing valuable pilot data on second line therapeutic approaches to inform future trials.

Assessments will be conducted up to 52 weeks post randomisation. The primary outcome measure is the Hand Eczema Severity Index at 12 weeks. Secondary outcome measures include modified Total Lesion Symptom Score, PGA, time to relapse, patient reported outcome measures and DNA extraction and assessment of genetic variants. A substudy on molecular inflammatory mediators will provide information on subgroup specific treatment responses. Photographs will be taken and HE severity assessed by a central review panel.

**Ethics and dissemination:**

Ethics approval was obtained from Leeds West Research Ethics Committee (14/YH/1259).Trial results will be disseminated at relevant clinical conferences and societies, published in peer-reviewed journals and through relevant patient groups.

**Trial registration number:**

ISRCTN80206075.

Strengths and limitations of this studyThe trial will directly compare treatment approaches used in clinical practice as first line treatment for severe hand eczema (HE), providing valuable data on their effectiveness which are not available at present.ALPHA takes disease subtypes and a range of factors into account known to influence response to treatment and will close an important knowledge gap on how to best treat patients with different morphologies, disease duration, allergy background and skin barrier composition with regard to filaggrin.This is the first interventional trial on severe HE which will compare different and previously used outcome measures for the assessment of severity meaning it will become possible to compare previous/other trials which have used different outcome measures.Clinical assessment of HE severity was completed by a blinded assessor, as delivery of psoralen combined with ultraviolet A and alitretinoin could not be blinded. The blinded assessor may change over time and within follow-up of the same patient; this will be reported during the final analysis.

## Introduction

### Background and rationale

Hand eczema (HE) is one of the most common skin disorders and an important cause of morbidity and occupational disability. It is estimated that up to 10% of the general population report HE at least once in a single year^1^ and 5%–7% of all patients with HE are estimated to develop severe chronic HE (CHE).^2^

The impact on daily life of sufferers is considerable.^3 4^ HE is characterised by severe itching and can be very painful and many studies have shown significant impairment of quality of life (QoL).^5 6^ HE is a persistent disease with a relapsing course and variable disease duration; in some cases at least 15 years of continuous HE have been reported.^6^

Uncertainty about the most effective treatment for HE is influenced by the fact that HE presents with several disease subgroups and underlying causes; and the natural course of HE often follows a recurrent pattern.^2 7^ The proposed classification in the UK^7^ and Europe^8^ defines atopic HE, allergic contact dermatitis and irritant dermatitis, either alone or in combination. However, discrimination of aetiologically distinct subtypes is a clinical challenge due to overlap/coexistence of different aetiologies.^7^

Moreover, it can be difficult to distinguish HE from some types of psoriasis or other skin conditions even on a histopathology level^9 10^ if patients present without involvement of other body sites and if the condition has already been treated with topical corticosteroids. Clinicians are aware of ‘mixed’ phenotypes named eczema-in-psoriatico or psoriasiform eczema^11^; which can be verified by skin biopsies, however it is not current practice to biopsy lesions in the UK. Samples obtained from the epidermis via tape stripping^12^ or washing,^13^ for example, contain markers such as IL-36, TARC, CCL20, TSLP, and IL-18 which have potential to identify eczema subtypes subtypes on a molecular level and thereby to improve subtype diagnosis.

Loss-of-function mutations in filaggrin, a protein important for the skin barrier, have been shown to be associated with atopic eczema.^14–18^ Experts have proposed^19^ that HE classification should consider filaggrin genotype for better subgrouping and potentially targeted treatment.

Alitrenoin (9-cis retinoic acid) is a naturally occurring vitamin A derivative (retinoid) and is the only licensed systemic agent for severe, CHE unresponsive to treatment with potent topical corticosteroids (National Institute for Health and Care Excellence, NICE TA177). However, there is a lack of controlled clinical trials that directly compare alitretinoin to other treatments as a first line therapy to demonstrate clinical effectiveness under daily practice conditions, which has been acknowledged by national and international expert groups.^20^

Our choice of comparator for alitretinoin was based on published clinical trials,^8^ and feedback from UK dermatologists, patients and the UK Dermatology Clinical Trials Network (UKDCTN). A survey conducted among 194 UK dermatologists informed the choice of immersion psoralen combined with ultraviolet A (PUVA) as the comparator treatment with both PUVA and alitretinion identified as popular first line therapies for severe hyperkeratotic and vesicular CHE.^21^

PUVA is used extensively across the National Health Service (NHS) and comprises a photosensitising agent in combination with UV-A. It is effective in both vesicular and hyperkeratotic HE.^22^ The photosensitising agent methoxsalen, 8-methoxypsoralen is used and the most common route of administration for this compound in the treatment of HE is topical (eg, gel, cream, immersion).^23 24^

The importance of topical PUVA was highlighted in a ‘consensus statement’ on the treatment of CHE^7^ as a widely used management option, although this is based more on clinical experience than on evidence.

Given the high socioeconomic impact of the disease and the pressing need for comparative studies on available first line treatments, ALPHA is a randomised controlled trial (RCT) comparing immersion PUVA and alitretinoin for the treatment of severe CHE.

## Methods and design

### Objectives

The overall aim of the trial is to determine the clinical and cost effectiveness of alitretinoin and immersion PUVA when used in conjunction with concomitant topical corticosteroids, emollients and patient education for the treatment of severe CHE which is unresponsive to treatment with potent topical corticosteroids alone.

The primary objective is to compare alitretinoin and immersion PUVA as first-line therapy in terms of disease activity at 12 weeks post planned start of treatment.

The secondary objectives are to compare alitretinoin to PUVA over 52 weeks postplanned start of treatment in terms of:

Disease activity over time.Time to relapse.QoL and patient benefit over time.Within trial and long-term cost-effectiveness.Safety.Educational need for patients.

Exploratory objectives are to:

Compare scoring systems Hand Eczema Severity Index (HECSI), modified Total Lesion Symptom Score (mTLSS), Dermatology Life Quality Index (DLQI) and physician’s global assessment (PGA) used to monitor treatment response.Explore whether response to first line treatment is affected by: duration of disease, clinical phenotype, disease severity, presence of atopy, smoking history, body mass index (BMI), foot involvement and Filaggrin loss of function mutation and other potential emerging mutations affecting skin barrier or response to treatment.Collect pilot data on clinical effectiveness of second line therapies.Explore treatment responses in HE subgroups defined by molecular inflammatory mediators.Compare alitretinoin and PUVA in terms of time in remission.Compare alitretinoin and PUVA in terms of nail assessment.Explore the use of the photography guide for patients from minority ethnic groups.

### Trial design

The ALPHA trial is a multicentre, prospective, open-label, two-arm parallel group, adaptive, RCT with one planned interim analysis.

A maximum of 780 consenting participants with severe CHE will be randomised on a 1:1 basis to receive either alitretinoin or PUVA in addition to concomitant topical corticosteroids, emollients and patient education. The trial is an adaptive design with a planned interim analysis to re-estimate the final sample size.

An internal pilot phase will inform on the feasibility of recruitment and delivery of the trial.

## Methods: participants, interventions and outcomes

### Trial setting and recruitment

Patients will be screened in UK secondary care dermatology outpatient, community hospital and general practice settings. Patients complete a self-screening questionnaire on the trial website and if eligible, will be invited to a formal eligibility assessment at one of the participating research sites which will take on the responsibility for seeking consent and undertaking trial research procedures. Formal eligibility assessment and recruitment will be undertaken in secondary care dermatology outpatient clinics.

### Eligibility criteria

Patients suffering with severe CHE and unresponsive to at least 4 weeks of treatment with potent topical corticosteroids will be assessed for eligibility in accordance with the criteria in table 1.

**Table 1 T1:** Eligibility criteria

Inclusion criteria	Exclusion criteria
Aged ≥18 years at the time of signing the informed consent form. Suffering from uncontrolled, severe CHE defined as the presence of *both* of the following criteria: (A) PGA score of severe.^27^ (B) Resistance to treatment with potent topical corticosteroids for ≥4 weeks prior to the point of eligibility screening. Provided written informed consent. Expected to comply with treatment and protocol schedule.	**Skin related:** Patients who have a clinically suspected infection (fungal, bacterial or viral) as cause for dermatitis of the hands. Patients with known clinically relevant allergic contact dermatitis of the hands unless they had made a reasonable effort to avoid the contact allergen. Patients suffering from atopic eczema covering more than 10% of body surface (excluding hands). Patients who have skin conditions worsened by the sun that is, do not tolerate UV-light (eg, lupus erythematosus, porphyria). **Treatment related:** Patients who have received phototherapy/photochemotherapy in the last 3 months prior to randomisation Patients who have received systemic vitamin A derivatives or other systemic immunosuppressants, for example, methotrexate or biologics treatment for HE in the last 3 months prior to randomisation. Patients who have received ciclosporin A or systemic glucocorticoid steroid treatment for HE within 1 week prior to randomisation. Patients receiving topical calcineurin antagonist treatment within 1 week prior to randomisation. Patients receiving concomitant treatment with tetracyclines, or medication with potential for drug–drug interaction with alitretinoin (eg, CYP3A4 inhibitor ketoconazole) that cannot be suspended or switched to an acceptable alternative Patients receiving concomitant treatment with relevant photosensitisers, when this treatment cannot be suspended for the duration of the intervention or switched to an acceptable alternative Patients with a history of melanoma skin cancer, or patients with a history of non-melanoma skin cancer depending on history, location and ‘severity’ of the non-melanoma skin cancer based on experience from routine practice. Patients who have received prior treatment with arsenic agents or ionising radiation in the treatment area (eg, hands). **General:** If female: (1) Lactating (2) Of childbearing potential (CBP): With positive pregnancy test (absence of pregnancy will be confirmed with a negative pregnancy test before randomisation). (2) Unwilling to follow pregnancy prevention programme measures* while receiving treatment and after the last dose of protocol treatment as indicated in the relevant SmPC. Patients with hepatic insufficiency (alanine aminotransferase and/or aspartate aminotransferase >2.5 times the upper limit of normal), known severe renal insufficiency, uncontrolled hyperlipidaemia (for all of the following: triglycerides, cholesterol and/or LDL cholesterol) or uncontrolled hypothyroidism in the 12 weeks period prior to randomisation. Patients with known hypersensitivity to peanut, soya or vitamin A derivatives or with rare hereditary fructose intolerance as determined by patient history. Patients currently suffering from hypervitaminose A as directed by clinical symptoms or patient history. Patients previously participated in the ALPHA trial.

Concomitant treatments not permitted are provided in online supplemental material 1.

*Rigorous contraception for people of CBP, unless exempt according to standard of care practice, is required 1 month before treatment, during the treatment period and 1 month after cessation of treatment as per usual standard practice.

CBP, child bearing potential; CHE, chronic HE; HE, hand eczema; LDL, low-density lipoprotein; PGA, physician’s global assessment; UV, ultraviolet.

10.1136/bmjopen-2021-060029.supp1Supplementary data

### Participant timeline

#### Consent

Blood samples are required to confirm eligibility and atopy status (presence/absence of specific IgE) prior to randomisation, and research sites have the option of using a one stage process to obtain informed consent for the full trial, or a two stage consent process with separate consent for the eligibility blood sample taken up to 12 weeks prior to randomisation.

Where eligibility is indicated, a full verbal explanation of the study and patient information leaflet will be provided by the attending clinical or research team. Patients will have as long as they need to consider participation and will be given the opportunity to discuss the trial with their family and other healthcare professionals before they are invited to take part.

For patients capable of providing consent but unable to sign or otherwise mark the consent from, witnessed consent will be provided by a carer, friend/family member or a local member of the clinical team independent of the research team. A copy of the consent form is provided in online supplemental material 2.

10.1136/bmjopen-2021-060029.supp2Supplementary data

#### Registration

All participants who consent will be registered (by an authorised member of staff at the trial research site) into the trial before any trial related procedures are performed, using the 24-hour automated registration telephone or web based system hosted by the Leeds CTRU.

#### Baseline assessment and randomisation

The baseline visit must be booked up to 7 days before the first PUVA appointment, within 12 weeks of the eligibility blood sample and after at least 1-month duration of the pregnancy prevention programme (if applicable).

At the baseline visit, eligible patients will be invited to provide informed consent for the full trial, photography sub study and biomarker sub study (for selected centres).

Eligible patients who provide full informed consent and complete the baseline assessments will be randomised into the trial by an authorised member of the research team at the site using the 24-hour telephone or web based randomisation service hosted by the Leeds CTRU.

#### Allocation

Patients will be randomised in a 1:1 allocation ratio, to receive either alitretinoin or immersion PUVA using a computer-generated minimisation programme incorporating a random element to ensure treatment groups are well balanced for the following participant characteristics: centre, diease duration (<6 months/6–24 months/>24 months), clinical phenotype (predominately hyperkeratotic/predominately vesicular/fingertip dermatitis), presence of specific IgE, DLQI (<15, ≥15), ethnicity (white/fair/dark).

If the participant is randomised to receive alitretinoin, the phototherapy department will be informed immediately that the PUVA treatment appointment will no longer be needed for this participant.

This randomisation service will also identify participants for participation in the biomarker and photography sub studies.

### Interventions

In both trial arms education on HE in using emollients, avoiding irritants and relevant contact allergens will be delivered in a standardised way prior to randomisation. The information material for participants will be based on sources used in clinical practice (British Association of Dermatology (BAD), National Eczema Society, Eczema Society patient information leaflets).

Topical corticosteroids may be used as required, as a reflection of standard clinical practice, however, it is recommended that they should belong to the ‘potent’ group.

#### Alitretinoin

Participants randomised to alitretinoin will be provided with a prescription dispensed as per standard care practice. It is anticipated that the patient will take the first dose of alitretinoin within 7 days of randomisation.

Prescriptions of alitretinoin can be written to allow up to 5 weeks supply of treatment, except people of childbearing potential following a pregnancy prevention programme whereby alitretinoin prescriptions should be limited to a 4-week supply.

According to standard clinical practice and NICE guidelines (TA177), alitretinoin will be self-administered at a starting dose of 30 mg, taken once daily with a meal for 12 weeks. After 12 weeks, participants will be assessed for their treatment response and depending on the outcome may continue alitretinoin for up to 12 more weeks.

Dose adjustment down to 10 mg or temporary cessation may occur according to standard practice in participants who suffer from related side effects such as headaches.

#### Immersion PUVA

Meladinine (methoxsalen) will be used in combination with UVA (PUVA). Meladinine 0.75% solution for local application in immersion PUVA is diluted to 3 mg/L (prepared by mixing 0.8 mL of 0.75% Meladinine solution in 2 L tap water). The participants hands are soaked for 15 min, followed by a maximum 30 min delay before UVA exposure. The UV-A radiation dose is individually tailored to the participant depending on phenotype (as per BAD guidelines^25^) and the erythematous response of the skin following treatment.

Calibration certificates for the UV-A machines are collected from centres prior to opening to ensure the same UV dose is administered across different centres.

Immersion PUVA will be administered twice weekly for 12 weeks in out-patient phototherapy departments and will be administered and supervised by specialised nurses/dermatologists according to local policy.

After 12 weeks of immersion PUVA treatment, participants will be assessed for their response to treatment and may continue immersion PUVA for up to 12 more weeks.

### Treatment pathway: criteria of response

Responders, defined as a PGA score of clear/almost clear at 12 weeks post planned start of treatment, will discontinue randomised treatment.

Partial responders, defined as a PGA score of mild/moderate at 12 weeks post planned start of treatment, will continue with randomised treatment for up to a further 12 weeks. During this second 12 weeks treatment period patients will be monitored at 4 weekly intervals and randomised treatment can be stopped at any time if the participant responds, or symptoms worsen and in the opinion of the treating clinician there is no clinical benefit to continuation.

Non-responders, defined as a PGA score of severe at 12 weeks post planned start of treatment, will discontinue randomised treatment.

In line with standard clinical practice, cessation or alteration of regimens at any time will be at the discretion of attending clinicians or the participants themselves. All randomised treatment will be discontinued at the maximum 24 weeks treatment period and participants will continue to receive ‘standard clinical practice’ and follow-up monitoring until the end of the follow-up period.

### Data collection

Clinical data and patient reported data will be collected at baseline, every 4 weeks to week 24 and 8 weekly thereafter to week 52. At each assessment a review of medication diaries will be conducted to obtain data on HE topical corticosteroid usage and any HE treatment received (in conjunction with clinical records review). Reportable adverse reactions will be collected and will exclude the following, providing they are non-serious, because they are known and common reactions; headaches and dry skin on regions of the body other than hands for alitretinoin, and mild to moderate erythema or itching of skin in PUVA treated skin locations for the PUVA arm). For participants recruited from October 2019, the follow-up period ends at 24 weeks post planned start of treatment. A full schedule of assessments is provided in online supplemental material 3.

10.1136/bmjopen-2021-060029.supp3Supplementary data

Data will be monitored for quality and completeness by the CTRU. Missing data will be chased until received, confirmed as not available or the trial is at analysis. Data received will be linked anonymised and entered onto a secure database at CTRU in accordance with the 2018 Data Protection Act. Photographs taken will be transferred immediately by secure email to CTRU and immediately deleted from the camera once confirmation of receipt is received by the research team. The CTRU and sponsor reserve the right to intermittently conduct source data verification exercises on a sample of participants, which will be carried out by staff from the CTRU or Sponsor.

Details of biological sample management is available in online supplemental material 4.

10.1136/bmjopen-2021-060029.supp4Supplementary data

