### Secondary endpoint analyses

Multivariable multilevel repeated measures linear regression models of log_e_(HECSI score), mTLSS, DLQI, PeDeSi and PBI-HE, and a multilevel repeated measures ordinal logistic regression model of the PGA over time will be fitted adjusting for the minimisation factors, covariates as for the primary endpoint analysis, corresponding baseline measurement and treatment group, as fixed effects. Centre, participant and participant-time interaction will be fitted as random effects. The parameter estimates, corresponding 95% CIs and p values will be reported; contrasts for the treatment effect at 24 and 52 weeks postplanned start of treatment will also be reported.

A Cox proportional hazards (PH) model (after confirming the PH assumption is valid) will be fitted to time to relapse adjusting for minimisation factors and covariates as for the primary endpoint analysis.

AEs and SAEs classified as related to treatment, HE or resulting from administration of any research procedures will be reported descriptively.

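### Adverse-reaction reporting exempts different non-serious reactions in each arm, so overall reaction counts and rates cannot be compared between alitretinoin and PUVA

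*Protocol article*

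**What the plan says.** All places are in the Protocol article.

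- **Objectives.** Safety is on the list introduced by "The secondary objectives are to compare alitretinoin to PUVA over 52 weeks postplanned start of treatment in terms of", so it is a comparison between arms.
- **Data collection.** Collection of reportable adverse reactions "will exclude the following, providing they are non-serious, because they are known and common reactions". The reactions named are "headaches and dry skin on regions of the body other than hands for alitretinoin, and mild to moderate erythema or itching of skin"; the second part reads in full "mild to moderate erythema or itching of skin in PUVA treated skin locations for the PUVA arm".
- **Alitretinoin.** Headache is the named example of a side effect behind treatment changes: "temporary cessation may occur according to standard practice in participants who suffer from related side effects such as headaches". The Immersion PUVA section likewise lets the skin's erythema influence the UVA dose.
- **Secondary endpoint analyses.** "AEs and SAEs classified as related to treatment, HE or resulting from administration of any research procedures will be reported descriptively". The exemption is not mentioned there.

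**The concern.** A comparison of harms needs the same events to be sought and recorded in both arms. Here the rule for what is recorded depends on the allocated treatment, and what is removed is, by the article's own reasoning, known and common. A table of treatment-related reactions by arm would therefore mix real differences with differences in what was collected.

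Descriptive reporting does not avoid this, because readers will set the two percentages side by side. Nor is it a detail that an analysis plan can supply later: an analysis can only use events that reached the database. At stake is what the trial may say about the relative tolerability of the two treatments. The primary outcome is not affected.

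**Working it through.** **Step 1: the rule by reaction and arm.** The article gives no reaction rate, so there is no stated figure to reproduce. The check is a reading of the Data collection rule. It assumes that each exemption applies only in the arm named, and that the event is judged a reaction to treatment.

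| Non-serious reaction | Alitretinoin arm | PUVA arm |
|---|---|---|
| Headache, any severity | exempt | reportable |
| Dry skin away from the hands | exempt | reportable |
| Mild to moderate erythema of the hands | reportable | exempt |
| Mild to moderate itching of the hands | reportable | exempt |
| Severe erythema of the hands | reportable | reportable |
| Any type not listed | reportable | reportable |

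The hands are the PUVA-treated site (Immersion PUVA section). Two differences follow from the text alone. First, the same symptom is treated in opposite ways in the two arms. Second, the severity limits differ: a severe but non-serious headache on alitretinoin is not reported, while severe but non-serious erythema on PUVA is.

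**Step 2: what this could do to a by-arm table (assumed rates).** Let q be the proportion of an arm with at least one reaction that is not exempt, and h the proportion with an exempt reaction, independent of each other.

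- True proportion with any reaction: 1 - (1 - q)(1 - h)
- Recorded proportion: q
- Share of affected participants who are recorded: q / [1 - (1 - q)(1 - h)]

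Take q = 0.20 in both arms and let h be 0.05, 0.15 or 0.30 in either arm.

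| h | True proportion | Recorded | Share recorded |
|---|---|---|---|
| 0.05 | 1 - 0.80 × 0.95 = 24% | 20% | 20/24 = 83% |
| 0.15 | 1 - 0.80 × 0.85 = 32% | 20% | 20/32 = 63% |
| 0.30 | 1 - 0.80 × 0.70 = 44% | 20% | 20/44 = 45% |

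The recorded difference, alitretinoin minus PUVA, is 20 - 20 = 0 points in every combination. The true difference is:

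- h = 0.05 for alitretinoin, 0.30 for PUVA: 24 - 44 = -20 points
- h = 0.05 and 0.15: 24 - 32 = -8 points
- h = 0.15 and 0.30: 32 - 44 = -12 points
- with the arms exchanged: +20, +8 and +12 points
- equal h in both arms: 0 points, although both arms are then under-recorded

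**Step 3: reading the result.** The recorded totals compare only the non-exempt reactions. They reflect the true overall difference when the exempt reactions add the same amount in both arms, and nothing in the article says that they do.

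**The case against.** The case for leaving this alone has real content.

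- **The choice is disclosed and reasoned.** The article states the exemption and why it was made. That stands, but the reason given, that the reactions are known and common, is also why their removal matters for a comparison.
- **Much safety information survives.** Serious reactions, severe erythema under PUVA and every unlisted type remain reportable in both arms, and no safety test is planned. A reader might infer that the trial cannot meet its safety objective at all. The text does not support that: SAEs and event types collected alike can still be compared.
- **Treatment changes may be recorded elsewhere.** Because headache is linked to dose adjustment, a reader might infer that reactions leading to dose changes leave no trace. The article does not show this. Diaries and clinical records are reviewed at each assessment for the hand eczema treatment received, and the full assessment schedule is in a supplement that is not shown. What is shown is only that such reactions are absent from the adverse-reaction data.
- **Hand itch is partly covered.** Itching is a feature of the disease, the Exploratory endpoints section uses the mTLSS for information on itch, and the severity scores have a blinded assessor in both arms. This weakens the point for itch. It does not help for headache or dry skin elsewhere.
- **Late changes to collection bring their own problem.** At submission 441 participants had been randomised. New symptom prompts would leave early and late participants recorded differently. This objection stands, and it is why the main remedy lies in the analysis and reporting.

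**Conclusion.** The point holds for overall reaction counts and rates: built as the article describes, they are not comparable between arms, and the planned safety report does not say so. This follows from the wording and needs no assumed rate.

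The size does rest on assumptions. With 20% of each arm having other reactions and 5% to 30% having exempt ones, independently, a recorded difference of 0 points is compatible with a true difference anywhere from -20 to +20 points, and between 45% and 83% of affected participants are recorded. Other rates would give other figures.

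A reader might infer from the missing severity limit on headache that alitretinoin's harms are understated the most. That is true only of the severity limit. The overall direction depends on how common the exempt reactions are in each arm, and the article does not give this. The consequence is a restriction on what may be concluded about one descriptive secondary objective.

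**What to change.** In the safety analysis and report:

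1. Limit between-arm statements to SAEs and to event types collected under the same rule in both arms. By the table above, severe erythema of the hands and unlisted types qualify; non-serious headache does not.
2. Report the exempted types separately, with the exemption and its arm stated beside them.
3. Present treatment changes and cessations due to reactions by arm, where treatment records hold them and their reasons.
4. State plainly that overall reaction counts and rates are not comparable between arms.

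The Objectives, Data collection, Alitretinoin, Immersion PUVA and Secondary endpoint analyses sections should be reconciled on this point. No view is taken here on any dose rule.

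Harmonising collection for the remaining participants is optional. Measured from 441 randomised, that is 500 - 441 = 59 at the minimum sample size and 780 - 441 = 339 at the maximum. If it is done, use the same symptom list and the same grade limits in both arms, and report results by collection period, so that a second difference in recording is not hidden.

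Items 1 to 4 cost almost nothing to carry out. The downside is a narrower safety claim; harmonised collection would add some data entry.
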